### Recruitment

gCJD patients will be recruited from the CJD clinic or the neurological department at the Tel Aviv “Sourasky” Medical Center (TASMC). Patients who are willing to participate will receive genetic counseling before signing informed consent. They will then be genotyped. Once their genotype is known they will be invited to participate in the study. HR of those patients will be invited to participate in the study if they fulfill the inclusion criteria. All potential participants will be approached by a neurologist who will explain the study procedures, the purpose, potential risks, and benefits of this study and informed consent will be obtained. TASMC serves as a hub for individuals who are suspected or diagnosed with gCJD, making it likely that the majority of gCJD patients in Israel are referred to TASMC. Additionally, Israel has maintained an official registry for all diagnosed gCJD patients since 1965. Patients who decline participation in the study but are seen at TASMC will still be documented in the registry.

### Sample size calculation and statistical analysis

With the objective of identifying biological markers for early detection of gCJD, we intend to conduct a comparative analysis of marker levels between gCJD patients and healthy individuals, as well as between healthy carriers and non-carriers. Based on the Israel National Registry for CJD, the annual incidence rate of CJD is 51 cases, although this is believed to be an underestimation. About two-thirds of the reported cases are familial cases, and of these cases, almost all are carriers of the E200K mutation. Given our conservative estimate that 50% of new cases of gCJD will be referred to our center, we anticipate that we will receive 15 new gCJD patients each year, for a total of 60 patients during the study period. Furthermore, we anticipate that approximately one-third of these patients, or 20 in total, will be willing to participate in the study.

With a conservative estimation of 3 first-degree HR per gCJD patient, this enables a population pool of > 100 per study period. As the E200K is an autosomal dominant mutation, 50% of the first-degree relatives of gCJD will carry the mutation. Based on Spudich et al. [34], the likelihood of developing gCJD is 0.45 in the age group of 51–60. According to Minikel et al., the average annual probability of onset (phenoconversion) for healthy carriers aged 40 to 80 years is 4.6% [35]. The primary aim of the study relates to biological markers for identifying phenoconversion. In our study, we referred to a positive CSF RT-QuIC.

CSF RT-QuIC has proven to be a relatively sensitive (73-97%) [13, 14] and a highly specific biomarker (99-100%) [12, 15–17] for diagnosing CJD, and it is now part of the standard diagnostic criteria [10]. Thus, considering a conservative estimate of a 13.6% phenoconversion rate among carriers (calculated as 3.4% expected conversion per year for 4 years) a sample size of 106 healthy relatives (53 carriers and 53 non-carriers) is required, based on a desired probability of type 1 error of 0.05 and a power of 80% (https://clincalc.com/stats/samplesize.aspx).

Secondary outcomes relating to the risk of phenoconversion will be also examined. With the objective of identifying risk factors for phenoconversion, we intend to conduct a comparison between groups (gCJD patients vs. HR), and within the HR group (carriers vs. non-carriers). We also intend to perform a Cox proportional hazards analysis. The analysis is based on the concept of hazard, which is a measure of the instantaneous risk of the event occurring at a given time. The Cox model assumes that the hazard for each individual is proportional to the hazard for others over time, and can be represented as a combination of individual-specific factors and their coefficients. The coefficients from the Cox model can be used to estimate the relative risk of phenoconversion for each factor, with larger coefficients indicating a greater risk of disease onset. By examining the relationship between the risk factors and phenoconversion time, Cox proportional hazards analysis can help identify which factors are most important in determining the risk of disease onset, allowing for the development of predictive models and the identification of potential targets for intervention.

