## Background

Creutzfeldt-Jakob Disease (CJD) is the most common prion disease in humans. It results from a conformational change of the normal prion protein (PrP^c^) into a pathological protein (PrP^sc^) that aggregates in the central nervous system [1]. Once formed, the initial PrP^sc^ oligomers can act as seeds for further misfolding of normal cellular PrP^c^ in a cascade that leads to neuronal death, as well as to the clinical manifestations of the disease.

Early symptoms are nonspecific and may include headaches, anxiety, and behavioral changes. Later, diffuse neurological impairment appears, including cognitive decline, cerebellar ataxia, pyramidal, and extrapyramidal deficits, disturbances of vision, and myoclonus. CJD can be etiologically classified into transmitted, sporadic (sCJD), and genetic forms (gCJD). The familial forms are caused by mutations in the PRNP gene that encodes for the prion protein (PrP). The largest cluster of gCJD cases exists in Jews of Libyan and Tunisian ancestry, carrying an E200K mutation (Glu to Lys substitution) in the *PRNP* gene. Approximately 200,000 Libyan Jews live in Israel, resulting in the largest population of at-risk individuals in the world [2].

The disease is invariably fatal, and survival is between several months to 1 year [3], with a mean survival from onset to death of 7.6 months [4]. Thus, by the time the disease is diagnosed, the neural pathology is extensive, and the neurodegeneration is vast. The presence of a genetic mutation may help identify individuals at risk for developing the disease as the penetrance of the mutation approaches 100% [5]. Carriers of the E200K mutation are born with this dominantly inherited mutation, but most remain asymptomatic until middle age, and some develop the disease as late as 80 years old [5].

E200K-PrP is initially formed as a normal PrP^c^ isoform [6]. Therefore, the mutation is not necessarily sufficient for the formation and accumulation of PrP^sc (6)^. This fact suggests that other, genetic and non-genetic factors affect the age at symptoms onset. The *CYP4 × 1* gene may influence the age at onset in patients with gCJD due to the E200K mutation and in sCJD [7]. Inheritance of gCJD with E200K mutation may exhibit anticipation (an earlier symptom onset or more severe presentation in offspring) [8]. However, this claim requires further investigation [9]. Other modifiers remain obscure.

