### Study population

Inclusion/ exclusion criteria.

gCJD patients’ inclusion criteria:

Diagnosis of CJD at baseline/ screening.Age 18 years or older at baseline.Confirmation of E200K mutation or willingness to undergo genetic testing as part of the pre-screening for new patients.Ability to provide written informed consent under Good Clinical Practice (GCP), International Conference on Harmonization (ICH), and local regulations, or having a person with a power of attorney willing to provide written informed consent.

gCJD patients’ exclusion criteria:

Any other medical or psychiatric condition or laboratory abnormality, which in the investigator’s opinion might preclude participation.Previously obtained MRI scan with evidence of clinically significant neurological disorder other than CJD.Current anticoagulant treatment (e.g. Non-vitamin K Antagonist Oral Anticoagulants (NOACs), Warfarin, Low Molecular weight Heparin) that might preclude safe completion of LP.Conditions that preclude the safe performance of LP, such as severe lumbar spinal disease, bleeding diathesis, or clinically significant coagulopathy or thrombocytopenia.Conditions that preclude the safe performance of MRI scannings such as subjects who have a pacemaker, aneurysm clips, artificial heart valves, ear implants, metal fragments or foreign objects in the eyes, skin, or body, or any other known contra-indication for MRI.Active malignant disease.

Healthy relatives (HR) inclusion criteria:

First–degree relative of an E200K gCJD patient.Age 50 years or older at baseline.Willingness to undergo genetic testing.Ability to provide written informed consent under GCP, ICH, and local regulations.Willingness and ability to comply with scheduled visits, required study procedures, and laboratory tests.

Healthy relatives’ exclusion criteria include a clinical diagnosis of CJD. Otherwise, exclusion criteria are the same as those described for gCJD patients.

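### The 50% carrier share holds at birth, not for relatives who are free of CJD at 50 or older, so 106 unselected relatives should contain fewer than 53 carriers

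*Protocol article*

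**What the plan says.** All statements are in the protocol article.

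- **Sample size calculation and statistical analysis.** After estimating the pool of healthy relatives, the text says that "50% of the first-degree relatives of gCJD will carry the mutation". It reports that "the average annual probability of onset (phenoconversion) for healthy carriers aged 40 to 80 years is 4.6" per cent. It then takes a lower rate for planning, "considering a conservative estimate of a 13.6% phenoconversion rate among carriers (calculated as 3.4% expected conversion per year for 4 years"), and concludes that "a sample size of 106 healthy relatives (53 carriers and 53 non-carriers) is required". The calculation uses a type 1 error of 0.05 and 80% power.
- **Study population.** A healthy relative must meet "Age 50 years or older at baseline", and a clinical diagnosis of CJD excludes. There is no upper age limit.
- **Background.** The disease is always fatal, onset runs from middle age to about 80, and "the penetrance of the mutation approaches 100" per cent.

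No section adjusts the 50% for carriers who are already affected or dead. None describes a genotype quota, carrier enrichment, or recruitment that continues until 53 carriers are found.

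**The concern.** The plan applies an onset rate forward, to predict conversions over four years, but not backward, to ask how many carriers are still healthy when they become eligible. Carriers leave the eligible pool through disease and non-carriers do not, so the pool tilts towards non-carriers, more so with age.

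Three things are at stake:

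- the 53/53 split as a description of what 106 relatives will yield;
- the number of relatives to genotype if 53 carriers are wanted;
- the amount of information in analyses that rest on carriers and on those who convert, namely the preclinical marker work and the Cox model for phenoconversion.

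**Working it through.** **1. Reproduce the plan's figure.** Inputs: 13.6% in carriers; 0% in non-carriers (my assumption, as the rate is not stated); two-sided 0.05 (sidedness is also not stated); 80% power; 1:1 allocation; no continuity correction. With a pooled null variance, the mean proportion is 0.068 and

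n = [1.96 × √(2 × 0.068 × 0.932) + 0.842 × √(0.136 × 0.864)]² / 0.136² = 52.6, so 53 per group and 106 in total (power 80.3%).

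The plan's arithmetic is sound. The point concerns the carrier share.

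**2. Share among eligible relatives.** Let S be the probability that a carrier is still unaffected at a given age. If half are carriers at birth, and death from other causes and participation do not differ by genotype,

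share = 0.5·S / (0.5·S + 0.5) = S / (1 + S).

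This equals 50% only if S = 1. Relatives needed to expect 53 carriers = 53 / share.

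**3. Onset assumptions.** With a constant annual rate h from age 40, S = (1 − h)^(age − 40). For the mild rows, onset starts at 50 and S is averaged over ages 50–60. The article's 0.45 likelihood at ages 51–60 does not say whether it is cumulative, so both readings are shown.

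| Assumption | S | Share | Carriers in 106 | Relatives for 53 carriers |
|---|---|---|---|---|
| Onset from 50, 3.4%/yr, ages 50–60 | 0.846 | 45.8% | 48.6 | 116 |
| Onset from 50, 4.6%/yr, ages 50–60 | 0.799 | 44.4% | 47.1 | 119 |
| 0.45 accruing evenly over 50–60 (mean S = 1 − 0.225) | 0.775 | 43.7% | 46.3 | 121 |
| 3.4%/yr from 40, all aged 50 | 0.708 | 41.4% | 43.9 | 128 |
| 4.6%/yr from 40, all aged 50 | 0.624 | 38.4% | 40.7 | 138 |
| 0.45 as cumulative risk | 0.55 | 35.5% | 37.6 | 149 |
| 3.4%/yr from 40, all aged 60 | 0.501 | 33.4% | 35.4 | 159 |
| 4.6%/yr from 40, all aged 60 | 0.390 | 28.1% | 29.7 | 189 |

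The binomial chance of at least 53 carriers among 106 is about 54% at a true 50% share, 22% at 45.8%, 5% at 41.4% and 1% at 38.4%.

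**4. Converters over four years.** The same rate must serve for depletion and conversion. Using the plan's additive method, 4 × 3.4% = 13.6% and 4 × 4.6% = 18.4%. The planned figure is 53 × 0.136 = 7.2.

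- 3.4% from age 40: 43.9 × 0.136 = 6.0 (age 50); 35.4 × 0.136 = 4.8 (age 60).
- 4.6% from age 40: 40.7 × 0.184 = 7.5 (age 50); 29.7 × 0.184 = 5.5 (age 60).
- Onset only from 50: 48.6 × 0.136 = 6.6; 47.1 × 0.184 = 8.7.

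At 4.6%, 53 carriers would give 53 × 0.184 = 9.8. At a given rate, converters therefore fall in the same proportion as carriers: 8–13% on the mild readings (48.6/53 to 46.3/53) and 17–44% with onset from 40 (43.9/53 to 29.7/53).

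**5. Power of the nominal comparison.** Take 40.7 carriers and 65.3 non-carriers at 13.6% v 0%. The pooled proportion is 0.136 × 40.7/106 = 0.0522. The null standard error is 0.0444 and the alternative standard error is √(0.136 × 0.864/40.7) = 0.0537. Then z = (0.136 − 1.96 × 0.0444)/0.0537 = 0.91, so power is 82%. Across the rows computed at constant rates it is 81–82%. It does not fall because no events are expected in non-carriers and that group grows as carriers shrink.

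**The case against.** Four points can be made for the plan.

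- **The only powered comparison is unharmed.** This stands. A reader might infer that fewer carriers leave the carrier v non-carrier test underpowered, but step 5 shows otherwise. The Cox analysis comes under secondary outcomes and carries no event target that the correction would break.
- **The onset curve is uncertain.** This stands in part. The 4.6% is an average over ages 40–80, not a flat rate from 40, and most carriers are said to stay well until middle age. On the mild readings the shortfall is 4–7 carriers, about the size of chance variation at a true 50% (SD = √(106 × 0.25) = 5.1). It is still a shift in the expected count, and none of these onset readings restores 50%.
- **A high onset rate partly offsets itself.** This stands. The rate that removes carriers before enrolment also makes the remaining ones convert faster. A reader might infer only about 4 converters, but that comes from depleting at 4.6% and converting at 3.4% (29.7 × 0.136 = 4.0), which is not coherent.
- **The split may be a requirement, not a forecast.** Relatives are genotyped, so recruiting to 53 carriers is possible, and the full protocol may provide for it. It therefore cannot be said that the trial will miss 53 carriers. But 106 would then be too few relatives to genotype, and the article places its flat 50% directly after the pool of healthy relatives.

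**Conclusion.** The statement is wrong as written. For relatives who must be free of CJD at 50 or older, the article's own onset and penetrance figures put the expected carrier share below 50%, so 106 unselected relatives should contain fewer than 53 carriers.

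The direction is certain on those figures; the size is not. It ranges from about 46–49 carriers on the mild readings to about 41–44 at age 50 and 30–35 at age 60 with onset from 40. With one rate throughout and onset from 40, expected converters are about 4.8–7.5 against the planned 7.2. With onset only from 50 at a constant rate they are 6.6–8.7. The 4.6% figures should be set against 9.8, not 7.2.

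This assumes constant rates, no onset before the stated starting age, participation and other mortality unrelated to genotype, and ages that the article does not report. Relatives over 60, who are eligible, would lower the share further.

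Severity is moderate. The consequence is for the stated split, the number to genotype and the precision of within-carrier analyses, not for the nominal power claim.

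**What to change.** Replace the flat 50% with the share conditional on being unaffected at the ages expected at enrolment. Then restate one of two things: the number of relatives to genotype in order to expect 53 carriers, or the carriers and converters expected from 106. Give the result as a range over stated onset assumptions, with the same rate for depletion before enrolment and conversion after it, and carry the event count into the Cox and marker analyses. If recruitment is to continue until 53 carriers are enrolled, say so.

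The cost is one recalculated passage with a less favourable figure; no new procedure is needed. If the larger number is chosen, check it against the pool: three relatives for each of the 60 anticipated patients is 180, and for the 20 expected to take part it is 60.

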The justification for the need for LP in this study is based on several factors. Firstly, CJD is a rapidly progressive disease, and early detection is critical for improving patient outcomes. The yearly analysis of the CSF may help identify prodromal changes in brain biomarkers, particularly the aggregation of PrP^sc^, which may indicate onset of disease before appearance of clinical symptoms. Secondly, the protocol has been granted approval by the ethics committee, taking into account the exceptionally high penetrance of the mutation and the valuable data that can only be obtained from CSF. This taken together with the fact that the LP procedure is considered safe led the committee to decide that its potential benefit outweighs the risk. Thirdly, participants who are not willing to repeat the LP procedure are not excluded from the study. However, in the event that they exhibit symptoms suggestive of conversion into the disease, an LP is carried out as part of the clinical diagnostic process. This ensures that participants are given the option to opt-out of the LP procedure while still receiving the necessary medical attention should they develop symptoms. In conclusion, there is a need for lumbar puncture in healthy carriers of the E200K mutation for CJD as part of a clinical trial studying the natural history of the disease and the prodromal phase. CSF sampling in a high risk healthy population is critical in order to identify markers associated with the prodromal phase of the disease and therefore was approved by the ethics committee. Participants who do not wish to undergo LP are not excluded and are able to participate in the study.

All gCJD patients will be scored according to the National Prion Monitoring Cohort (NPMC) Scale (MRC Prion Disease Rating Scale) [36], which is a multimodal scale assessing both cognitive impairment and daily function disability. This scale consists of 11 parameters: bowel function, bladder function, toilet use, bathing, feeding, transfer and mobility, stairs, best verbal response, memory and orientation to surroundings, judgment and problem-solving, and use of tools. Each section is scored between 0 and 4 with 0 indicating complete disability and 4 normal ability, for a maximum of 20 points.

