## Discussion

This project aims to identify biological markers of preclinical CJD and risk factors for phenoconversion. The relatively large and homogeneous cohort of healthy carriers of the E200K mutation, as well as the longitudinal design and comprehensive protocol, should allow for better characterization of the preclinical phase of gCJD. The prospective clinical and behavioral data may also help to identify environmental risk factors for phenoconversion. The long follow-up increases the possibility of phenoconversion during the study period, which is crucial for the identification of both early markers of disease and risk factors. In other neurodegenerative diseases, such as Parkinson’s disease, validated criteria for the diagnosis of early or prodromal disease exist [46]. The results from this study may contribute to the establishment of similar criteria for prodromal CJD and identifying the “window of opportunity” for preventive interventions.

There are several disease-modifying drugs under development in different phases of pre-clinical and clinical trials. These treatments will likely need to be given at the very early stages of the disease before significant neurodegeneration occurs, or even to healthy individuals at-risk for phenoconversion.

The continuous follow-up of the participants and the frequent assessments (every 6 months for 4 years) will allow early identification and diagnosis in case of conversion into disease. Identifying gCJD patients at the very early clinical or even prodromal phase could also facilitate their enrollment in future clinical trials for disease-modifying drugs. The knowledge generated from this study is likely to advance the understanding of the underlying clinicopathological processes that occur at the very beginning of CJD, as well as potential genetic and environmental risk factors for the development of the disease, therefore advancing the development of safe and efficient interventions.

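### The 13.6% four-year conversion risk adds annual risks instead of compounding them, so 53 per group falls short of the size needed for 80% power

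*Protocol article*

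**What the plan says.** All the inputs are in the protocol article, in the section on sample size calculation and statistical analysis.

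- **Planning rate:** "a conservative estimate of a 13.6% phenoconversion rate among carriers", with the derivation in brackets: "calculated as 3.4% expected conversion per year for 4 years".
- **Resulting size:** "a sample size of 106 healthy relatives (53 carriers and 53 non-carriers) is required", for a "desired probability of type 1 error of 0.05" and 80% power, with an online calculator as the source.
- **Background rate:** the section also cites a source according to which "the average annual probability of onset (phenoconversion) for healthy carriers aged 40 to 80 years is 4.6"%. This is not the value used for sizing.
- **Follow-up:** the Discussion gives assessments "every 6 months for 4 years", which matches the multiplier of four.

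The section does not state the rate assumed in non-carriers, the sidedness, the test, or how 3.4% was obtained.

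**The concern.** The rate is given per year and is multiplied by the number of years. That is valid only if the same share of the original cohort converts each year. The section speaks of onset as an annual probability for healthy carriers, and the planned Cox analysis treats phenoconversion as a time-to-event outcome. On that footing the risk applies each year to those who have not yet converted, and a sum of annual risks overstates the four-year risk.

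The 13.6% is the only effect size behind the stated sample size and power. The 53 per group is the rounded-up minimum for 80% power, and the calculation shows no allowance for missing cerebrospinal fluid, although "participants who are not willing to repeat the LP procedure are not excluded from the study". Even a small overstatement therefore takes power below its target.

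**Working it through.** **Inputs.** Annual risk 3.4%, four years, type 1 error 0.05, power 80%, 53 per group: all from the protocol. Assumptions: 0% in non-carriers and a two-sided test, because these reproduce the published number.

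**Formula** (pooled two-proportion, no continuity correction), with p̄ = (p1 + p2)/2:

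n per group = [1.960·√(2p̄(1 − p̄)) + 0.8416·√(p1(1 − p1) + p2(1 − p2))]² / (p1 − p2)²

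**Step 1: reproduce the plan's figure.** p1 = 0.136, p2 = 0, p̄ = 0.068.

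- 1.960 × √0.12675 = 0.6978
- 0.8416 × √0.11750 = 0.2885
- n = (0.9863)² / 0.018496 = 52.6, so 53 per group and 106 in total. Power at 53 is 80.3%.

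Other settings do not give 53: one-sided gives 42, continuity correction 67, unpooled variance 50, and a 1% non-carrier rate 66.

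**Step 2: compound the risk.** 1 − (1 − 0.034)^4 = 1 − 0.8708 = 0.1292.

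**Step 3: same formula, corrected input.** p1 = 0.1292, p2 = 0, p̄ = 0.0646.

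- 1.960 × √0.12087 = 0.6814
- 0.8416 × √0.11252 = 0.2823
- n = (0.9637)² / 0.016698 = 55.6, so 56 per group and 112 in total.

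**Step 4: power at the planned 53 per group.** z = (0.1292 × √53 − 0.6814) / √0.11252 = 0.773, so power is 78.0%.

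**Step 5: expected conversions among 53 carriers.** 53 × 0.136 = 7.2; 53 × 0.1292 = 6.8.

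**Step 6: other readings of the annual figure.**

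| Reading | Four-year risk | n per group | Power at 53 |
|---|---|---|---|
| Added, as in the plan | 13.6% | 53 | 80.3% |
| Annual probability, compounded | 12.9% | 56 | 78.0% |
| Constant hazard, 1 − exp(−0.136) | 12.7% | 57 | 77.3% |
| 73% of the compounded 4.6%: 0.73 × (1 − 0.954^4) | 12.5% | 58 | 76.6% |

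The last row tests a possible origin of the 3.4%, discussed in the objection.

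**Step 7: dependence on the test.** With no events in non-carriers and 53 per group, Fisher's two-sided test needs 6 v 0 (p = 0.027; 5 v 0 gives p = 0.057). The uncorrected chi-square needs 4 v 0. Exact power:

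| Test | At 13.6% | At 12.9% |
|---|---|---|
| Fisher, P(X ≥ 6) | 74% | 70% |
| Uncorrected chi-square, P(X ≥ 4) | 94% | 92% |

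**The case against.** **The meaning of 3.4% is not stated.** The wording about an annual probability of onset belongs to the 4.6%. The 3.4% is only called expected conversion, and it follows the sentence on RT-QuIC sensitivity. It may be the 4.6% scaled by the lowest quoted sensitivity (0.73 × 4.6% = 3.36%), which is an inference. If it meant a fixed share of the original cohort each year, adding would be correct. What stands is that the authors should define it. But the text does not give the fixed-share meaning, and under the 73% reading compounding gives 12.5%, slightly worse than 12.9%. A higher sensitivity would give a larger figure, but then 3.4% would not be the annual input.

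**The planning rate is still conservative.** Compounding the cited 4.6% gives 17.2%, for which 41 per group suffice and 53 give about 90% power. That is true, and 12.9% remains well below it. But the plan chose to size on 3.4%, and the stated power should follow from that input.

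**The effect is small, and exact tests do not turn on it.** Fisher's test is below 80% and the chi-square above it at either rate, and 56 per group still gives only 75% under Fisher. This also stands. It shows that the 80% target is tied to the approximate formula, which is why the test needs naming.

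**The non-carrier rate matters more.** The quoted specificity of 99–100% allows a 1% positive rate in non-carriers. That alone raises the size to 66 per group with the added risk, or 71 with the compounded one. This is correct, but it does not make 13.6% right.

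**Conclusion.** The point holds. The four-year risk is a sum of annual risks. On the plan's own 3.4% and the formula that reproduces its figure, the size for 80% power is 56 per group (112), not 53 (106), and 53 per group give 78.0%. The shortfall is 3 per group, 6 in total, or 5.7% of 106.

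This rests on three assumptions: 3.4% is an annual probability among carriers not yet converted, non-carriers have no events, and the calculation is the two-sided pooled formula. The first fits the section's language and the planned Cox analysis, and a constant hazard gives nearly the same answer. The second and third are inferred from the match to 53.

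The error is modest and casts no doubt on the study design. It should be corrected because the published size and power statement rests on it.

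**What to change.** In the sample size section, say what the 3.4% represents. If it is an annual probability, replace the 13.6% with 12.9%, shown as 1 − (1 − 0.034)^4. Then either:

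- keep 106 relatives and report about 78% power, or
- give 56 per group (112 in total) for 80% power.

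In the same sentence, name the test, its sidedness and the rate assumed in non-carriers. If an exact test is intended, calculate power for that test, because 56 per group does not reach 80% under Fisher.

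The first option costs one corrected figure and a slightly less favourable power statement, with no change to conduct or enrolment. The second adds six relatives to the target.

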## Design and methods

### Study aims

To identify biological markers of preclinical CJD and risk factors for phenoconversion.

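### The 80% power behind the 106 relatives belongs to a carrier versus non-carrier contrast in conversion, not to the primary aim of markers that identify phenoconversion

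*Protocol article*

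**What the plan says.** Under Study aims, the protocol article sets two aims: "To identify biological markers of preclinical CJD and risk factors for phenoconversion". The section on sample size and statistical analysis narrows the first: "The primary aim of the study relates to biological markers for identifying phenoconversion". It continues: "In our study, we referred to a positive CSF RT-QuIC". It quotes a sensitivity of 73–97% and a specificity of 99–100% for that assay in diagnosing CJD.

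The calculation then starts from "a conservative estimate of a 13.6% phenoconversion rate among carriers (calculated as 3.4% expected conversion per year for 4 years") and concludes that "a sample size of 106 healthy relatives (53 carriers and 53 non-carriers) is required". Alpha is set at 0.05 and the target power at 80%. The equal split fits the statement that "50% of the first-degree relatives of gCJD will carry the mutation". The same section also quotes an average annual probability of onset of 4.6% for carriers aged 40 to 80.

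The conversion rate in non-carriers and the sidedness of the test are not printed. The section gives no marker difference, SD, target sensitivity, hazard ratio or event count. For markers, the declared comparisons are of marker levels, between patients and healthy individuals and between healthy carriers and non-carriers. Cox regression is announced under secondary outcomes.

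**The concern.** The only rate entered is the rate at which carriers develop the disease. Set against a non-carrier rate of about zero, the test asks whether carriers convert and non-carriers do not. The Background already attributes familial CJD to *PRNP* mutations and says that "the penetrance of the mutation approaches 100"%. That contrast is close to a premise of the study.

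The primary aim needs something else: evidence that a marker separates carriers who convert from carriers who do not. The text passes from the primary aim, through RT-QuIC, to the 106 as though one followed from the other. A reader could then credit the marker work with 80% power that was never calculated for it.

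**Working it through.** **Inputs from the sample size section.** Carriers: 3.4% × 4 years = 13.6%. Groups: 53 and 53. Alpha 0.05, power 80%. RT-QuIC sensitivity 73–97%. Alternative onset rate 4.6% per year. **Inferred:** about 0% in non-carriers and a two-sided test.

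**1. Reproducing 106.** Two proportions, pooled variance under the null, 1:1 allocation:

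n = [z₁ √(2p̄(1−p̄)) + z₂ √(p₁(1−p₁) + p₂(1−p₂))]² / (p₁−p₂)²

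with z₁ = 1.960, z₂ = 0.842, p₁ = 0.136, p₂ = 0 and p̄ = 0.068:

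- z₁ term: 1.960 × √0.12675 = 0.698
- z₂ term: 0.842 × √0.11750 = 0.289
- n = 0.986² / 0.0185 = 52.6, so 53 per group and 106 in total; power at 53 is 80.3%

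Variants tried that do not match:

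| Variant | Per group |
|---|---|
| One-sided, 0% in non-carriers | 42 |
| One-sided, continuity-corrected | 56 |
| Two-sided, continuity-corrected | 67 |
| Two-sided, 0.1% in non-carriers | 54 |
| Two-sided, 0.5% in non-carriers | 59 |
| Two-sided, 1% in non-carriers | 66 |

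**2. If the endpoint is RT-QuIC positivity.** Multiply the conversion rate by the quoted sensitivity and keep 0% in non-carriers:

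| Sensitivity | Positive carriers | Power at 53 per group | Per group for 80% |
|---|---|---|---|
| 73% | 0.136 × 0.73 = 9.9% | 66% | 74 |
| 97% | 0.136 × 0.97 = 13.2% | 79% | 55 |

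This assumes that only converters turn positive and that diagnostic sensitivity carries over to them.

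**3. Expected converters among 53 carriers, with full follow-up.**

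- Article's rate: 53 × 0.136 = 7.2
- 3.4% per year, compounded: 53 × (1 − 0.966⁴) = 6.8
- 4.6% per year, compounded: 53 × (1 − 0.954⁴) = 9.1

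**4. What those events support.** For one covariate in a Cox model restricted to carriers, the hazard ratio detectable with 80% power at two-sided 5% is exp(2.80/√D) per SD of a continuous covariate, and exp(2.80/√(D/4)) for a factor split 50/50, where D is the number of events.

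| D | Per SD | 50/50 factor |
|---|---|---|
| 6.8 | 2.9 | 8.5 |
| 7.2 | 2.8 | 8.1 |
| 9.1 | 2.5 | 6.4 |

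**5. Marker levels, single measurement, two-sample t-test, 80% power at two-sided 5%.**

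- Carriers versus non-carriers, 53 versus 53: 0.55 SD
- Converters versus other carriers, 7 versus 46: 1.16 SD

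**The case against.** The strongest defence is that the article names its endpoint. If RT-QuIC positivity is compared between healthy carriers and non-carriers, with conversion as the anticipated positivity rate, a difference would say something about a marker in people enrolled as healthy. This stands in part: it would be wrong to say that the powered comparison could yield no marker information. But the rate entered is then unadjusted for sensitivity, which lowers power to 66–79%, and positivity by genotype still does not test whether the marker separates carriers who convert from those who do not.

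A reader might go further and infer that 106 relatives serve neither aim. The documents do not support that. Carriers versus non-carriers is a declared comparison for both the marker and the risk-factor objectives, and 53 versus 53 is a usable size for a marker level. Nor does the article claim 80% power for the Cox work, which it places under secondary outcomes.

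Two further reservations stand. The non-carrier rate is deduced from the match, so the reconstruction is an inference, though a tight one. And the 1.16 SD comes from a single-time-point t-test, whereas the article plans repeated-measures models, so it is a guide only.

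**Conclusion.** The arithmetic of 106 is sound for 13.6% versus about 0%. What is wrong as written is the aim to which its 80% is attached. On the conversion reading, the power covers a contrast by genotype that the study largely presupposes. On the RT-QuIC reading, it is about 66–79%, not 80%. On neither reading does it describe the ability to find markers that identify conversion among carriers, which rests on about 7 to 9 events.

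The conclusion depends on the inferred non-carrier rate. The event counts assume that all 53 carriers are followed for four years. Restricting the Cox model to carriers is an assumption of this review; the article does not say which relatives enter it. The sample itself is not shown to be inadequate for comparing marker levels by genotype; its power for that is simply not stated. This should be fixed, but it does not call the design into question.

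**What to change.** Reword the sample size section; no participants, visits or procedures are added.

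1. Print the non-carrier rate and the sidedness. Say that the 80% applies only to 13.6% versus 0% by genotype. For RT-QuIC positivity, give 66–79% power at 53 per group.
2. State that 53 versus 53 detects about 0.55 SD in a single marker, at two-sided 5% with 80% power, before any adjustment for the number of markers.
3. State that about 7 converters are expected (about 9 at 4.6% per year), so that a one-covariate Cox model within carriers has 80% power only for a hazard ratio of about 2.5–2.9 per SD, or about 6.4–8.5 for a 50/50 factor. Label the within-carrier marker and risk-factor analyses as exploratory estimation, reported with confidence intervals.

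The cost is a less favourable statement of what the study can show.
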